#### Secondary analysis

3.1.3.

##### White matter injuries

3.1.3.1.

The correlation between the age at surgery (in number of days of life) and the presence of WMIs (yes vs. no) will be assessed by describing and comparing age at surgery according to the presence and absence of WMIs. Non-contrast 3 Tesla MRIs with 3D-T1 weighted and axial T2-weighted sequences and diffusion-weighted images will be performed. Qualitative and quantitative analyses of the MRIs will be done using a lesion score as previously reported in the literature (3, 20, 21); specifically, acquired brain injuries will be characterized as (i) cerebral vascular accidents, (ii) white matter injuries (WMI), (iii) intraventricular hemorrhages (IVH), or (iv) global hypoxic-ischemic injury (HI).

The severity of the injuries will be assessed as follows: 0 = normal, 1 = minimal lesion (minimal WMI and IVH grade I-II), 2 = cerebral vascular accident (any cerebral vascular accident), and 3 = moderate or severe lesion (moderate or severe WMI, IVH III, or HI).

Finally, we will assess the severity of the WMIs using the quartered point system (QPS) (21), the volumetric measurement and the categorical scale described by Miller et al. (20) as normal (no lesion), minimum (≤3 WMI, each <2 mm), moderate (>3 WMI or WMI measuring >2 mm, but <5% of the hemisphere in question), or severe (>5% of the affected hemisphere). The same patient may present several brain injuries, which could also be bilateral. The most severe lesion will be retained for the lesion score.

A comparison test for quantitative data will be used. A Student's t-test will be used if the application conditions are met; the non-parametric Mann-Whitney test will be used otherwise. The correlation between the age at surgery (in number of days of life) and the severity of WMI (four levels of severity, including normal) will be conducted using a comparison test for quantitative data. The analysis of variance will be used if the application conditions are met; otherwise, the non-parametric Kruskal-Wallis test will be used.

These analyses will be conducted on the data collected from the MRIs performed in both the preoperative and postoperative phases.

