Neurological	• Ischemic cerebrovascular accident • Hemorrhagic cerebrovascular accident	• Epileptic seizure • Cerebral thrombophlebitis
Surgical	• Recurring diaphragmatic paralysis/paresis • Definitive AV block with device • Acute hemorrhaging requiring revision surgery	• Cardiac tamponade • Unplanned revision surgery • Chylothorax

There is no consensus regarding the optimal age for surgery in terms of morbidity and neurodevelopmental outcomes, and its definition is a real challenge. Importantly, at the present time, there are no established rules for determining the timing of surgery in our department. For the most common CHD types, the TGA are corrected during the first ten days of life. There is a more pronounced degree of variation for HLHS. This common practice won't be changed for our observational study.

Our aim is to determine the relationship between surgical timing and long-term neurodevelopmental outcomes for various types of complex CHD. Similarly to Anderson et al. (15) with postoperative morbidity, we aim to determine a cut-off point for surgical timing that will improve neurodevelopmental outcomes. For each type of CHD, we aim to determine a cut-off for surgical timing based on postoperative morbidity and neurodevelopmental outcomes. We hope that our findings will contribute to the development of surgical timing guidelines in the future.

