### Procedure overview

2.5.

Each recruited patient will participate in the study for 24 months (Figure 1). Following the recruitment (visit 0, V0) conducted in the neonatal period before cardiac surgery, a preoperative brain MRI will be performed before surgery (visit 1, V1) if the health of the neonate allows for this. During the 15 days following the surgery, a postoperative brain MRI is performed (visit 2, V2). Visits 1 and 2 aim to assess preoperative brain injuries and those that appear or worsen postoperatively. The preoperative MRI should not delay cardiac surgery. Visits 3 (V3), 4 (V4), and 5 (V5) will involve neurodevelopmental assessments at 4 months, 12 months, and 24 months, respectively, conducted by a single child neurologist ([name]) and the Alberta Infant Motor Scale (AIMS) assessment at 4 months and 12 months. These assessments will be scheduled and conducted during conventional follow-up cardio-pediatric appointments. During visit 5 (V5), at 24 months, a standardized neuropsychological assessment will be performed using the Bayley-IV test.

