#### Sample size

3.1.1.

Two previously published studies that reported a significant correlation between age at surgery and the incidence of WMIs included 26 and 37 patients, respectively (7, 8). Based on the active file of patients with complex CHD operated on each year in Cardiac Surgery at the La Timone Enfants Hospital, the total number of subjects included will be 100. With this number of 100 included patients and according to the values of (i) a 5% bilateral alpha risk and (ii) 80% statistical power, we estimate the minimum correlation coefficient between age at surgery and Bayley-IV test scores as 0.39.

According to the same hypotheses (5% bilateral alpha risk and 80% statistical power), and based on the intended number of patients recruited for each (Clancy) CHD subtypes, the minimum correlation coefficient that could be highlighted between age at surgery and Bayley-IV test scores is:
*r* = 0.38 for class I, two-ventricle heart without arch obstruction (*n* = 50)*r *= 0.65 for class II, two-ventricle heart with arch obstruction (*n* = 15)*r* = 0.76 for class III, single ventricle heart without arch obstruction (*n* = 10)*r* = 0.53 for class IV, single ventricle heart with arch obstruction (*n* = 25)”

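### White matter injury on the preoperative MRI is compared by age at a later operation, so any postponement after an abnormal scan can bias the result towards the hypothesis

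*Protocol article*

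**What the plan says.** In the statistical section on white matter injuries, the link between age at surgery and WMI "will be assessed by describing and comparing age at surgery according to the presence and absence of WMIs". Presence is tested with Student's t or Mann-Whitney, and the four severity levels with analysis of variance or Kruskal-Wallis. The section ends: "These analyses will be conducted on the data collected from the MRIs performed in both the preoperative and postoperative phases". The section on moderating factors then enters age at surgery as the explanatory variable in logistic models with presence of WMI as a dependent variable.

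On how the surgery date arises, the Introduction states that "there are no established rules for determining the timing of surgery in our department". It gives a usual window for one diagnosis only ("the TGA are corrected during the first ten days of life") and describes more variation for hypoplastic left heart syndrome. Eligibility runs to surgery within the first 2 months of life.

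Two statements bear on the gap between scan and surgery. The Procedure overview says "The preoperative MRI should not delay cardiac surgery", and the Brain MRI section places the preoperative scan immediately before the operation without giving an interval.

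**The concern.** Preoperative WMI is fixed once the scan is done. Age at surgery is fixed only when the operation takes place. Days between the two cannot have contributed to a lesion already visible, but the planned comparison counts them as exposure. If the gap were the same for everyone this would be harmless. If it is longer for infants whose scan was abnormal, infants with WMI will be older at surgery because of the finding, and the arrow runs the wrong way.

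The direction is what makes this worth correcting. The study hypothesises that earlier surgery reduces perioperative WMI, and postponement after a finding pushes the comparison the same way, so it could be taken for confirmation. WMI on the two MRIs is the first secondary objective and part of the proposed mechanism. The postoperative comparison is less exposed, but the article does not restrict it to new lesions, so a lesion already seen before surgery can be counted there too.

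**Working it through.** **No plan figure to reproduce.** The article gives no power or effect size for WMI. Its only whole-cohort figure concerns the Bayley-IV: "we estimate the minimum correlation coefficient between age at surgery and Bayley-IV test scores as 0.39". By Fisher's z with a two-sided 5% level and 80% power, tanh((1.960 + 0.842)/√97) = 0.277 at n = 100, so 0.39 does not reproduce. That is a separate matter and does not enter here.

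**Order of events.** Preoperative scan (outcome seen), then surgery (exposure fixed). The analysis treats the second as explaining the first. This follows from the text and needs no simulation.

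**Inputs from the documents.** n = 100 ("the total number of subjects included will be 100"); 5% two-sided test; days 1-10 as the usual window for transposition only; surgery up to 2 months for the cohort.

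**Assumptions, because the documents give no values.** Preoperative WMI in 20-30% of infants; no true effect of age on WMI; a fraction f of infants with WMI postponed by d days after the scan; several distributions of planned age.

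**Mean shift.** Under no true effect, the expected difference in age at surgery (WMI minus no WMI) is f × d.
- f = 0.10, d = 5: 0.10 × 5 = 0.5 day
- f = 0.25, d = 5: 0.25 × 5 = 1.25 days

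**Shift relative to the spread of age.** For a uniform distribution the SD is range/√12. For the 1.25-day shift:
- days 1-10: SD 9/√12 = 2.6; 1.25/2.6 = 0.48 SD
- days 1-30: SD 29/√12 = 8.4; 1.25/8.4 = 0.15 SD
- days 1-60: SD 59/√12 = 17.0; 1.25/17.0 = 0.07 SD

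The same postponement therefore matters much more in a narrow window than in a wide one.

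**Simulated false-positive rate, n = 100, Mann-Whitney at 5%, d = 5 days.**

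| Planned age | f = 0.25 | f = 0.10 |
|---|---|---|
| Uniform, days 1-10, whole cohort | 30-37% | 9-10% |
| Uniform, days 1-30 | 8-10% | 5-6% |
| Half days 1-10, half days 1-60 | 8-10% | about 5% |
| Uniform, days 1-60 | 5-7% | about 5% |

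An intermediate case (mean 10 days, SD 6, n = 100) gives, for f = 0.25, 7-9% with a 3-day delay and 20-28% with a 7-day delay. With f = 0.10 and 3 days it stays at about 5%.

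**Check of the remedy.** With no postponement, or with age taken before any postponement, the rate returns to about 5% in every scenario. Age at the preoperative scan has this property because a later change of date cannot alter it.

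**The case against.** The strongest reply is that the path is not documented. The article does not say when the scan is reported, who sees it, or that a result has ever moved an operation. Reporting workflow is the kind of detail an article leaves to the full protocol. The reasons it names for delaying surgery are low weight and haemodynamic instability, not MRI findings. It also says the scan should not delay surgery and is done immediately beforehand; if both hold, age at scan and age at surgery nearly coincide and the change of variable alters little. Finally, the stated secondary objective is framed in terms of age at surgery.

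Most of this stands, and it limits the point to a conditional risk. It does not remove it. The instruction that the scan should not delay surgery can be read as concerning the procedure alone; it does not say that a finding cannot change the date. Placing the scan just before surgery describes the intention, and the gap would widen for exactly those infants who are then postponed.

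A reader might infer more than the documents support:
- **That the surgical team is unmasked and acts on the scan.** The only blinding mentioned concerns the data analysis; silence on the rest establishes nothing either way.
- **That the design produces a false confirmation.** That needs fairly frequent or long postponement, which is neither reported nor planned.
- **That rejection of 30% or more is to be expected.** That needs a window given only for transposition to apply to all 100 infants.
- **That the Bayley-IV correlation and age threshold are distorted in the same way.** No calculation supports this. Injured infants being operated on later would be confounding of that analysis, a different question, and multivariable models with prognostic factors are planned.

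**Conclusion.** The point holds as a conditional weakness of one analysis. For preoperative WMI, the chosen exposure includes time after the outcome was observed, and nothing in the article rules out that the length of this time depends on the outcome. Any resulting bias favours the hypothesis.

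Its size cannot be known from the documents. With 10-25% of infants with WMI postponed by 5 days at n = 100, the false-positive rate is about 5-10% for a cohort with a wide age range and 9-37% if every operation fell within days 1-10. Eligibility up to 2 months makes the wider ranges more plausible for the whole cohort, so the effect there is probably modest; it would be larger in a subgroup with a narrow window, other things equal. All these figures rest on assumed WMI prevalence, postponement rate, delay and age distribution. Because the correction is cheap and postponement would be hard to separate from a true timing effect if it were not recorded, the change is worth making.

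**What to change.** In the white matter injury section, and in the corresponding logistic model:

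1. For WMI on the preoperative MRI, use age at that MRI as the exposure, for both presence and severity. Age at surgery can stay as a secondary description, to match the stated objective.
2. For WMI on the postoperative MRI, keep age at surgery.
3. Record for each infant whether the surgery date was moved after the preoperative scan result.
4. Repeat the WMI comparisons without the infants whose date was moved, as a sensitivity analysis.

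The cost is one changed variable, using a date the study already generates, one data item and one extra analysis. No procedure is added and decisions on surgical timing are unaffected. If no date was moved, the record shows it and the reverse path is closed.

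This does not deal with common causes: haemodynamic instability can, on the article's own account, both delay surgery and foster brain injury. That remains for the adjusted models.

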### Secondary objectives

1.3.

The secondary objectives of our study are to evaluate the correlation between age at surgery (days of life) of neonates with complex CHD and the following outcomes:
i.the presence and severity of WMIs observed on preoperative and postoperative brain MRI;ii.postoperative morbidity;iii.the duration of the postoperative hospital stay;iv.neurodevelopmental outcomes, including clinical pediatric neurological assessment (4 months, 12 months, and 24 months) and functional motor skill assessment using the Alberta Infant Motor Scale (AIMS; 4 months and 12 months).We will also assess the moderating role of demographic characteristics and pre-, intra-, and postoperative factors on the following outcomes:
i.the frequency of pre-, and postoperative WMIs;ii.postoperative morbidity;iii.neurodevelopmental outcomes, including clinical pediatric neurological assessment (4 months, 12 months, and 24 months), functional motor assessment using the AIMS (4 months and 12 months), and the Bayley-IV test (24 months).

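### WMI severity is an ordered scale but is tested against age at surgery with methods that ignore the order, and the postoperative analysis does not separate new or worsened lesions

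*Protocol article*

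**What the plan says.** Section 1.3 (Secondary objectives) lists, first among the outcomes to be correlated with age at surgery, "the presence and severity of WMIs observed on preoperative and postoperative brain MRI".

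Section 3.1.3.1 (White matter injuries) grades WMI as normal, minimum, moderate or severe. It then describes a correlation between age at surgery and "the severity of WMI (four levels of severity, including normal", and fixes the test: "The analysis of variance will be used if the application conditions are met; otherwise, the non-parametric Kruskal-Wallis test will be used". It names no trend test, rank correlation or ordinal model for severity. Section 3.1.3.4 models only the presence of WMI, by logistic regression, so the omnibus comparison is the only severity analysis stated.

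On the two scans, section 3.1.3.1 says: "These analyses will be conducted on the data collected from the MRIs performed in both the preoperative and postoperative phases". Section 2.5 (Procedure overview) gives their purpose: "Visits 1 and 2 aim to assess preoperative brain injuries and those that appear or worsen postoperatively". Section 2.6 (Brain MRI) repeats that purpose and places the second scan within 15 days after surgery.

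**The concern.** With four groups, ANOVA and Kruskal-Wallis are tests on 3 degrees of freedom. They ask whether age at surgery differs anywhere among the grades. Shuffling the grade labels leaves the p-value unchanged, and neither test yields a coefficient or a direction. The study's hypothesis is directional: earlier surgery should mean less WMI. A test that uses the order puts all its power on that question, whereas the omnibus test spreads it over patterns nobody has proposed. The article calls its own sample relatively small (section 5), and WMI is the proposed mechanism, so the loss matters.

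The second issue is interpretation. If the postoperative variable is simply the WMI visible on the second scan, a lesion that predates surgery and persists counts on both scans. An association with age that arises entirely before surgery could then be read as one with postoperative injury.

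**Working it through.** **Inputs from the article (section 3.1.1).** "the total number of subjects included will be 100"; "a 5% bilateral alpha risk and (ii) 80% statistical power".

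**Assumed, because the documents do not give them.** The split of infants across WMI grades, the strength of the age-severity link, and the rates of preoperative, new and resolving lesions.

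**The plan's own figure.** The article states no power for WMI severity. Its only whole-cohort figure concerns another outcome: "we estimate the minimum correlation coefficient between age at surgery and Bayley-IV test scores as 0.39". Fisher's z gives r = tanh((1.960 + 0.842)/√(100 − 3)) = tanh(0.284) = 0.277, so 0.39 is not reproduced; it corresponds to about 50 patients. That is a separate matter and does not affect this point.

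**Step 1, analytic power.** A 1-df test at two-sided 5% has 80% power when the noncentrality is (1.960 + 0.842)² ≈ 7.85. With the same noncentrality on 3 df, power is 64%. Where the 1-df test has 90%, the 3-df test has 78%. For 80% power the 3-df test needs a noncentrality of 10.90, and 10.90/7.85 = 1.39, or about 39% more patients. This step needs no severity split, but it assumes that all the signal lies along the ordered trend.

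**Step 2, simulation at N=100.** A four-level grade was given a monotone latent link to age (1,000 to 3,000 runs per setting).

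| Assumed split (normal/minimum/moderate/severe, %) | Latent correlation | Kruskal-Wallis | Spearman | Gap (points) |
|---|---|---|---|---|
| 60/20/12/8 | 0.25 | 37.2% | 54.9% | 17.7 |
| 60/20/12/8 | 0.30 | 50.5% | 69.2% | 18.7 |
| 60/20/12/8 | 0.35 | 68.4% | 83.5% | 15.1 |
| 40/25/20/15 | 0.2 | 26.9% | 40.6% | 13.7 |
| 40/25/20/15 | 0.3 | 60.5% | 76.2% | 15.7 |
| 40/25/20/15 | 0.4 | 87.4% | 95.6% | 8.2 |
| 25/25/25/25 | 0.2 | 28.4% | 42.1% | 13.7 |
| 25/25/25/25 | 0.3 | 64.6% | 79.8% | 15.2 |
| 25/25/25/25 | 0.4 | 89.4% | 96.6% | 7.2 |

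Across four splits, from 70/15/10/5 to equal quarters, at correlation 0.3 with normally distributed age, Kruskal-Wallis has 47–65% power and Spearman 66–80%. ANOVA, the plan's first choice, does slightly better than Kruskal-Wallis at 51–68%, against 69–82% for a linear trend. With no association, every test rejects in about 5% of runs.

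**Step 3, carry-over to the postoperative scan.** Assumptions: preoperative WMI in 20–40% of infants with a latent correlation of 0.4 with age, and new WMI in 15–35% with no relation to age. Tested by Mann-Whitney, any WMI on the postoperative scan is significantly related to age in 29–74% of runs if no lesion resolves, and in 19–46% if 30% resolve. New WMI alone is significant in about 4–5%. The first result is a true association with total lesions; it misleads only if read as postoperative injury.

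**The case against.** The strongest reply is that this is inefficiency and not error. The planned tests hold their type I error, the endpoint is secondary, and no power is claimed for it. All of that stands.

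The ordered test gains only if the relation is monotone. The study also looks for a cut-off or an optimal window, and an omnibus test does not presuppose a trend. This is a fair reason to keep the omnibus comparison as support. It is not a reason to make it the only severity test when the stated aim is a correlation and the stated hypothesis is directional.

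The WMI objective also does not rest on this test alone. The plan compares age by WMI presence with a t-test or Mann-Whitney test. Under the 60/20/12/8 split, Mann-Whitney on presence has 50%, 64% and 78% power at correlations 0.25, 0.30 and 0.35, against 56%, 70% and 85% for Spearman on severity in the same runs, a gap of 6 to 7 points. That limits the harm to the objective as a whole, but it leaves the severity question with the weaker test.

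Two stronger readings are tempting, and the documents do not support them:

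- A reader might infer from the 0–3 lesion score, in which a stroke scores 2, that stroke could be scored as WMI severity. Section 3.1.3.1 presents that score as severity of injuries in general, then turns to WMI with its own scale, and specifies the test for WMI severity with a level called normal. At most a cross-reference is missing.
- A reader might infer that the postoperative result will largely repeat the preoperative one. The article does not say how the postoperative variable is coded, counting total lesions would agree with the objective in section 1.3, and the degree of repetition depends on an unknown persistence rate.

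**Conclusion.** The point holds as a matter of efficiency on a secondary endpoint. The severity scale is ordered and the aim is a correlation, yet the fixed tests use neither the order nor a direction. Under a monotone relation, 80% power falls to about 64% analytically. At N=100 the simulated loss of Kruskal-Wallis against Spearman is roughly 7 to 19 points, and a little less for ANOVA. The size of the loss rests on assumed severity splits and correlations. That some power is lost rests only on the relation being monotone, which is what the study hypothesises.

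The postoperative point is smaller. The stated analyses do not carry through the purpose that sections 2.5 and 2.6 give for the paired scans. The carry-over figures show what could happen under assumed lesion rates and are not a forecast for this cohort.

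**What to change.** In section 3.1.3.1, make Spearman's rank correlation with a 95% confidence interval the test of age at surgery against WMI severity on the normal/minimum/moderate/severe scale, and name that scale explicitly. A proportional-odds model with age at surgery as covariate would serve equally. Keep ANOVA or Kruskal-Wallis as descriptive support. Spearman is already the fallback for Bayley-IV and AIMS (section 3.1.2) and for length of stay (section 3.1.3.3), so nothing new is introduced. The cost is some loss of sensitivity to a non-monotone pattern, which the retained omnibus comparison partly covers.

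For the postoperative MRI, analyse WMI that is new or worse than on the preoperative MRI, or adjust for the preoperative grade, and report total postoperative WMI as support. This needs both scans from each infant. The loss should be small, because section 2.1 describes a cohort with both scans and section 2.3 appears to exclude infants lacking either. No extra scans are needed.
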